### Exercise PRO-MS

In the proposed Exercise PRO-MS study an extensive set of neurodegenerative biomarkers will be used to investigate the effect of two patient-tailored exercise programs, i.e. PRT and high intensity interval training (HIIT) on neurodegeneration in people with PMS. Both resistance and endurance training might affect neurodegeneration but currently it is unknown whether one intervention is more beneficial than the other one. In the proposed study we will examine the effectiveness of both interventions on neurodegeneration in the PMS population.

The primary aim of this trial is:

To examine whether PRT and HIIT can slow down neurodegeneration in people with PMS. We expect that participants will benefit from both PRT and HIIT as compared to no training.

Additional objectives of the Exercise PRO-MS study are:
To determine whether PRT and HIIT can improve patient functioning in people with PMS.To explore the relationships between patient functioning on the one hand, and biomarkers related to neurodegeneration on the other hand.To determine the relative responsiveness of neurodegeneration outcome measures, and to explore effect sizes of between-intervention comparisons.To determine whether cardiovascular risk factors improve as a consequence of a PRT or a HIIT intervention.

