## Methods/design

### Design and setting

A single-blind monocenter randomized phase II trial with extended baseline will be conducted from 2020 till 2023 at the MS Center Amsterdam (MSCA), The Netherlands. MSCA is embedded in the Amsterdam UMC, location VUmc, and is a specialized center for MS care, research and education. In an extended baseline design, participants function as their own control reducing variance and increasing power. During intake participants will be assessed for eligibility for inclusion. In case of inclusion, participants will be scheduled for two baseline measurements sixteen weeks apart. After the second baseline measurement participants will be randomized to either the PRT or HIIT group. Measurements will be repeated post-intervention and after a 16-week follow-up period.

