### Sample size calculation

Based on pre- and post-intervention measurements, paired analysis will be performed to examine the effect of exercise per type of intervention. Power calculation was performed using data from a previous study examining the effect of a 24-week progressive resistance training (group difference of 0.3 PBVC, standard deviation (SD) 0.5, estimated effect size 0.6) [7]. A sample size of 24 achieves 80% power with a significance level of 0.05. With an estimated drop-out of 15% we will include 30 participants per group.

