#### Primary objective

Within-group paired analysis will be performed for whole brain atrophy measured with PBVC at three different time intervals (difference between baseline 1 and 2, difference between baseline 2 and post- intervention and difference between post-intervention and follow-up) using linear mixed models The analysis will be performed separately for the two different exercise programs. The analysis will be performed using an intention-to-treat method, including all randomized participants, regardless of adherence and measurement completion. Secondary, per protocol analysis will be performed for further exploration of the intervention effects. In addition, one model for the total group of participants with the two different exercise programs as a determinant, will be explored.

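### The primary models are fitted separately per programme, so each training-versus-run-in contrast leaves out the other arm's pre-randomisation data and is less precise than it could be

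*Protocol article*

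**What the plan says.** The primary aim, in the section Exercise PRO-MS, sets each programme against no training: "We expect that participants will benefit from both PRT and HIIT as compared to no training". The no-training reference is the 16-week extended baseline, which Design and setting justifies by precision: "In an extended baseline design, participants function as their own control reducing variance and increasing power". Allocation follows it: "After the second baseline measurement participants will be randomized to either the PRT or HIIT group".

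The Primary objective section then fixes the analysis: "Within-group paired analysis will be performed for whole brain atrophy measured with PBVC at three different time intervals", using linear mixed models, and "The analysis will be performed separately for the two different exercise programs". It closes with a further model: "In addition, one model for the total group of participants with the two different exercise programs as a determinant, will be explored".

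The sample size section uses the same per-programme paired analysis, with a "group difference of 0.3 PBVC, standard deviation (SD) 0.5, estimated effect size 0.6", and concludes: "A sample size of 24 achieves 80% power with a significance level of 0.05".

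**The concern.** The run-in PBVC is measured before anyone is allocated. Randomisation therefore makes its expected value the same in the two arms, and any observed difference between the arms' run-in means is chance. Two separate models estimate this one quantity twice, each time from half of the randomised participants. For PRT versus no training the HIIT arm's run-in plays no part, and the reverse holds for HIIT.

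The extended baseline was chosen to reduce variance, and separate fitting gives up part of that benefit. At stake is the width of the confidence interval and the power of the two contrasts that answer the primary aim, in a trial planned at 80% power for each programme.

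**Working it through.** **Inputs from the protocol article.** Difference 0.3 PBVC, SD 0.5, effect size 0.6, 24 evaluable per group, significance level 0.05 (Sample size calculation). Randomisation after week 16 (Design and setting). Separate models (Primary objective).

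**Assumed, because the article does not give them.** Equal PBVC variance s² in each interval, a common correlation r between intervals within a person, and a two-sided test.

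**1. The plan's own figure.** Paired t-test, n = 24, SD of the paired contrast 0.5:
- SE = 0.5/√24 = 0.1021
- noncentrality = 0.3/0.1021 = 2.94
- power with 23 df = 80.4%

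The stated 24 reproduces when 0.5 is read as the SD of the contrast.

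**2. Variance with separate models** (training minus own run-in, n per arm):

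2s²(1 − r)/n

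**3. Variance with one common run-in mean.** Let T be the arm's training mean, R its run-in mean and R̄ the run-in mean over both arms. The joint model estimates the contrast as (T − rR) − (1 − r)R̄. The first term is uncorrelated with the run-in data, so

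s²(1 − r²)/n + (1 − r)²s²/(2n) = s²(1 − r)(3 + r)/(2n)

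**4. Ratio of step 3 to step 2:** (3 + r)/4, a variance reduction of 25% × (1 − r). It is below 1 for every r < 1. A simulation of 20,000 trials at r = 0.3 gave 0.833 against 0.825 from the formula.

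**5. Size on the plan's inputs** (contrast SD 0.5, n = 24, separate SE 0.1021, separate power 80.4%):

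| r | Variance ratio | SE ratio | Joint SE | Power, 23 df | Power, 46 df |
|---|---|---|---|---|---|
| −0.4 | 0.650 | 0.806 | 0.0823 | 93.7% | 94.6% |
| 0 | 0.750 | 0.866 | 0.0884 | 90.1% | 91.3% |
| 0.5 | 0.875 | 0.935 | 0.0955 | 85.3% | 86.8% |
| 0.8 | 0.950 | 0.975 | 0.0995 | 82.3% | 83.9% |

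The two df values bracket what a joint model might use. Moving from 23 to 46 df with no change in variance would by itself raise 80.4% to 82.1%, so the 23 df column shows the gain due to variance alone.

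**6. Where r may lie.** Run-in and training intervals share the week-16 scan. Error in that scan enters them with opposite signs and lowers r, while stable differences between people in atrophy rate raise it. If 0.5 were the SD both of one interval and of the contrast, then 2(1 − r) = 1 and r = 0.5.

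**7. Comparison that does not gain.** For training versus follow-up the variance ratio is 1.00 under equal correlation.

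**8. Pooling without modelling the covariance.** Subtracting the pooled run-in mean from the training mean gives a ratio of (1.5 − r)/(2 − 2r): 0.75 at r = 0, 1.00 at r = 0.5 and 1.75 at r = 0.8. The gain needs a model that keeps the within-person correlation.

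**9. Price.** The two contrasts share R̄, with covariance (1 − r)²s²/(2n) and correlation (1 − r)/(3 + r): 0.33 at r = 0, 0.14 at r = 0.5 and 0.05 at r = 0.8.

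**The case against.** The plan is coherent as it stands. Design rationale, sample size and analysis all rest on each participant as own control within a programme, and the power claim reproduces. Enrolling 30 per arm with 15% dropout leaves 30 × 0.85 = 25.5, which gives about 82% (n = 25) to 84% (n = 26). There is no concurrent untrained group, so keeping the two programme results statistically independent is a defensible preference. A shared run-in lets one chance error move both. If r is high, the gain is small. All of this stands, and it limits the point to efficiency.

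Three stronger readings are tempting, and the article supports none of them.
- *The primary analysis is biased or underpowered because of separate fitting.* It is unbiased and delivers its stated power on its stated inputs.
- *Half of the no-training data is thrown away, and half of the precision with it.* The other arm's run-in is only absent from each programme's primary contrast. It serves its own arm, and a total-group model is planned. Doubling the run-in data cuts the SE by about 13% at r = 0, not by half.
- *Every primary comparison suffers.* The section lists three intervals, and training versus follow-up gains nothing under equal correlation.

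The planned total-group model does not remove the point. It is to be explored, so it does not carry the primary inference, and the text does not say that the run-in mean is common. With a separate run-in mean for each arm it would largely reproduce the separate contrasts. Its exact parametrisation may be left to an analysis plan, but the article itself settles which analysis is primary.

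**Conclusion.** The point holds as an avoidable loss of precision in the two training-versus-run-in contrasts. Under equal interval variances, the SE of each could be lower by about 13% at r = 0, 6% at r = 0.5 and 3% at r = 0.8, and by more if r is negative. The direction is certain for any r below 1. The size is not, because the article does not give r. The power figures also depend on reading 0.5 as the SD of the contrast, which is the reading that reproduces the planned 24. The change is worth making because it needs no extra participant or scan, but the trial's primary analysis would remain valid without it.

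**What to change.** In the Primary objective section, make the total-group linear mixed model the primary analysis, fitted to all randomised participants with:
- one common mean for the pre-randomisation interval (weeks 0-16);
- programme-specific means for the training and follow-up intervals;
- a modelled within-person covariance, for example unstructured, rather than simple subtraction of a pooled run-in mean.

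Name two primary contrasts: PRT training minus common run-in, and HIIT training minus common run-in. Keep the separate per-programme models as a sensitivity analysis.

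The cost is wording in the analysis section. The statistical price is the correlation of (1 − r)/(3 + r) between the two contrasts, which should be reported with the results so that two favourable findings are not read as independent confirmation.

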#### Additional objectives

Longitudinal assessment of change in the different outcome measurements will be determined using a linear mixed model over four different time points. The relationship between (change in) patient functioning measures and (change in) neurodegeneration will be assessed using multiple regression analyses. The relative responsiveness of the various neurodegenerative biomarkers will be analyzed by relating the smallest real difference to the minimally important change of the outcome measures and comparing the area under the receiver operation characteristics curves [74]. Domain-specific patient perceived effect parameters will be used as an anchor. To analyze the effects on cognitive performance, a Reliable Change Index (RCI) will be calculated based on the mean and standard deviation of the healthy controls to adjust for learning effects [75]. An RCI of ±1.64 (90%) will be considered a significant improvement/decline.

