##### Cognition

The Brief International Cognitive Assessment for MS (BICAMS) will be used to examine information processing speed and immediate verbal and visual recall [52]. The BICAMS consists of the Symbol Digit Modalities Test (SDMT), California Verbal Learning Test-II (CVLT-II) and the Brief Visuospatial Memory Test-Revised (BVMT-R). Parallel versions will be used to avoid learning effects. Fifteen healthy controls will also be included and followed over the same 48-week time span to be able to correct for learning effects in the analysis.

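### The cognitive change cut-off of ±1.64 is labelled 90%, but with the mean and SD taken from 15 healthy controls its expected false-flag rate is about 13.5%, not 10%

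*Protocol article*

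**What the plan says.** The Cognition section of the protocol article names three tests: "The BICAMS consists of the Symbol Digit Modalities Test (SDMT), California Verbal Learning Test-II (CVLT-II) and the Brief Visuospatial Memory Test-Revised (BVMT-R"). It adds a reference group: "Fifteen healthy controls will also be included and followed over the same 48-week time span", whose purpose is to allow a correction for learning. Under Additional objectives the article says that "a Reliable Change Index (RCI) will be calculated based on the mean and standard deviation of the healthy controls to adjust for learning effects", and it sets the decision rule: "An RCI of ±1.64 (90%) will be considered a significant improvement/decline".

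The article therefore fixes the cut-off, its confidence label, the source of the standardisation and the size of that source. It does not print the formula of the index, and it mentions no small-sample adjustment.

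**The concern.** ±1.64 is the two-sided 90% limit of a standard normal variable. It applies to a person's standardised change when the population mean and SD of change are known. When both come from a small sample, the standardised change of a new, truly stable person has heavier tails and a wider spread than the normal. On average, more than 10% of stable people then fall outside ±1.64.

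Two things follow. First, the 90% attached to the word significant is not what the rule delivers on average. Second, every patient is compared with the same 15 controls, so the error in the control mean and SD is common to all of them and does not average out over 60 participants. An error in the control mean also has a direction. If the control mean is off by one standard error (1/√15 = 0.26 SD) and the SD is exactly right, false flags are about 8.4% in one direction and 2.9% in the other. Sampling noise in the controls could then look like improvement or decline in the patients.

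**Working it through.** **Inputs from the protocol article**
- Cut-off ±1.64, labelled 90% (Additional objectives). The implied false-flag rate is 10% two-sided, 5% per direction.
- Mean and SD taken from the healthy controls (Additional objectives).
- n = 15 controls (Cognition).
- 60 randomised participants (Abstract, Methods).

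**Assumptions, not in the article**
- Index = (patient change − control mean change) / control SD of change.
- Change scores are normal, which the 90% label itself needs.
- Stable patients have the same mean and SD of change as controls.
- All 15 controls complete, unless stated otherwise.

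**Step 1: the plan's own figure.** With known mean and SD, 2 × P(Z > 1.64) = 0.101. The label is right for that case; the extra 0.1 point comes from rounding 1.645 to 1.64.

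**Step 2: mean and SD estimated from n controls.** The numerator has variance σ²(1 + 1/n) and the denominator is an SD with n − 1 degrees of freedom. So index / √(1 + 1/n) follows t with n − 1 degrees of freedom.
- n = 15: √(16/15) = 1.0328 and 1.64/1.0328 = 1.588. Then 2 × P(t₁₄ > 1.588) = 0.1346, or 6.7% per direction. One million simulated control samples also gave 13.46%.
- n = 12: √(13/12) = 1.0408 and 1.64/1.0408 = 1.576. Then 2 × P(t₁₁ > 1.576) = 0.143.
- n = 10: 0.152.

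**Step 3: does the result hang on the assumed formula?**

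| Reading, n = 15 | Expected rate at ±1.64 |
|---|---|
| Only the mean is uncertain | 11.2% |
| Only the SD is uncertain | 12.3% |
| Both uncertain (Step 2) | 13.5% |
| Control baseline SD with a known test-retest correlation | 13.5% |
| As above, correlation also estimated from the 15 | about 15% |

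All of these exceed 10%.

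**Step 4: the rate for one realised control sample.** Over simulated samples of 15 controls, the rate at ±1.64 has a median of 12.0% and a 95% range of 2.8% to 31.9%. It exceeds 10% in 62% of samples. The main source is the SD: its 95% confidence factors with 14 degrees of freedom are 0.73 and 1.58.

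**Step 5: size in patients.** If all 60 were stable and assessed, 60 × 0.135 = 8.1 would be flagged against 60 × 0.10 = 6. That is about 2 more per test and interval, or about 1 per direction.

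**Step 6: the cut-off that gives 10% on average.** t₁₄(0.95) × √(16/15) = 1.761 × 1.0328 = 1.82. For 12 controls it is 1.87. At ±1.82 with 15 controls, the realised rate still has a 95% range of about 1.5% to 27%.

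**The case against.** The strongest reply is that ±1.64 is the conventional limit and 90% its conventional label. The article states no false-flag rate, and the exact formula may stand in the full protocol or the analysis plan, which are not shown. That is fair as far as it goes. The label is correctly derived for a known mean and SD, so this is not a slip of arithmetic. But the article itself fixes the limit, the label and the 15 controls, and each reading of the index tried above gives more than 10% on average.

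Three stronger readings are tempting, and the documents do not support them.
- A reader might infer that the actual rate in this trial will be 13.5%. That figure is an average over possible control samples. The trial will have one sample and one rate, which cannot be known in advance.
- A reader might infer that the error always runs towards declaring change. In about 38% of control samples the rate falls below 10%. The bias holds on average only.
- A reader might infer that nothing in the design can offset the error, because there is no untrained patient group. The article has a 16-week period without intervention before randomisation, with cognition measured at both ends (Design and setting; Table 2). The same index can be calculated for that interval in the same patients, and both arms use the same controls. The offset may be incomplete if control norms are estimated separately for each interval, but it cannot be ignored.

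It is also true that the index serves an additional objective, and that the linear mixed models planned for change over the four time points do not use this cut-off. The primary brain volume analysis and the sample size are untouched.

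**Conclusion.** The point holds in a limited form. With 15 controls, a cut-off of ±1.64 has an expected two-sided false-flag rate of about 13.5%, so the 90% label overstates the confidence by about 3.5 percentage points on average. The exact figure rests on the assumed form of the index, on normality, on complete follow-up of the controls and on stable patients varying as controls do. Other forms of the index move it between 11% and 15%.

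The larger practical issue is imprecision: the trial's own rate could plausibly lie anywhere from about 3% to 32%. The consequence is modest, since it affects how many individuals are called improved or declined in a secondary part of the study. It merits a correction of wording and method, and does not threaten the main conclusions.

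**What to change.** Either of two changes would do.
1. Replace ±1.64 by t(0.95, n − 1) × √(1 + 1/n), which is ±1.82 for 15 controls, recomputed for the number of controls who complete. If the index is not change minus control mean change over the control SD of change, derive the limit for the formula used.
2. Keep ±1.64 for comparability with other studies, call the 90% nominal, and state the expected rate of about 13.5% with 15 controls.

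In both cases, print the formula and report the proportions improved and declined with intervals that carry the uncertainty of the control mean and SD. This matters because ±1.82 corrects only the average rate. It also gives 10% only if stable patients vary as controls do: if, for illustration, their SD of change were 20% larger, ±1.82 would give about 16%. It would also help to show the same proportions for the untrained baseline interval.

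The cost is a line or two of analysis text, with no new data or visits. Under the first change slightly fewer patients are classified as changed, and comparability with studies that use ±1.64 is slightly reduced. More controls would also reduce the problem (expected rate 11.1% with 50), but at a real cost that an additional objective may not justify.

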### Study status

Currently, participants are being recruited (May 2020).

## Discussion

In PMS neurodegeneration plays a key role in the progression of disability. Up to date there are no DMTs affecting the non-inflammatory drivers of the disease. Previous studies in animals, healthy aging people, and people with MS indicate that exercise training might result in neuroprotective effects and reduced neurodegeneration. However, the interventions used varied, study groups were heterogeneous and sample sizes were most often too small. In this study, the effect of two exercise interventions, PRT and HIIT, will be specifically examined in a homogeneous cohort of people with PMS. Both training interventions are expected to induce neuroprotective effects. Currently it is not known which intervention is more beneficial. In this trial a large variety of neuroprotective outcome measures will be assessed, such as structural and functional imaging parameters of the brain but also biomarkers in blood. In addition, several patient functioning measures will be assessed, for example mobility, dexterity and cognition. Also, the preventive effect of exercise on patient’s cardiovascular risk will be studied. The combination of all these outcome measures is one of the major strengths of this study and will hopefully give better insight in the neuroprotective effect of high intensity exercise programs in people with PMS.

In the proposed study we will examine the biomarkers BDNF and sNFL. However, a lot of ongoing research is examining new possible biomarkers for PMS. For example, Glial Fibrillary Acid Protein (GFAP), Vascular Endothelial Growth Factor (VEGF) and sContactin1 and 2. GFAP is a major intermediate cytoskeletal protein of astrocytes and an increase in levels of GFAP is associated with more astrogliosis [76, 77]. VEGF plays a key role in angiogenesis and seems to play a role in neurogenesis [78, 79]. sContactin1 and sContactin2 are potential biomarkers for axonal dysfunction [80]. However, the research on biomarker development is still ongoing and future research might unveil other, more specific neurodegenerative biomarkers. Therefore, participants will be asked to donate some extra blood for possible future analyses.

## Data Availability

Data sharing is not applicable to this article as no datasets were generated or analyzed during the current study. Datasets (generated and/or analyzed) during the proposed study will be available from the corresponding author on reasonable request.

